### 2.2. Study Groups

The control group will include patients with recent moderate–severe sleep apnea (1–3 months) undergoing treatment with continuous positive airway pressure (CPAP) therapy. An initial ultrasound measurement of the tongue genioglossus fat will be made and 3 months after inclusion in this study.

The MT group will include patients with moderate apnea. MT exercises alone, once a day for 3 months, will be performed exclusively via the AirwayGym app. An initial ultrasound measurement and drug-induced sleep endoscopy (DISE) will be performed with repeated control at 3 months.

In the MT-CPAP severe apnea group, patients will use CPAP at night, measuring the number of hours they use it at night. A new sleep study will be performed at 3 months. An initial ultrasound measurement and DISE will be made with control at 3 months (Figure 1).

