### 4.1. Sample Size

Calculation of sample size

No studies have reported on the influence of MT on the reduction in cervical fat in patients with sleep apnea and evaluations of obstruction patterns in DISE before and after. Our study will initially be a pilot study, with 15 patients in the control group, 15 patients in the moderate MT apnea group, and 15 patients with MT-CPAP severe apnea.

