### 4.3. Assessments

Patients will be jointly evaluated by the pulmonology and otorhinolaryngology services of the hospital.

Evaluation by a pulmonology specialist: A detailed medical history is taken to record symptoms and risk factors associated with sleep apnea. BMI is calculated, and questionnaires that assess daytime sleepiness (the Epworth test; Appendix A) and sleep quality (the Pittsburgh questionnaire; Appendix B) are administered. Patients suspected of having sleep apnea undergo either polysomnography or diagnostic respiratory polygraphy based on their clinical symptoms. After this first assessment, the pulmonologist refers the patient to the otorhinolaryngology department to assess the anatomy and functionality of the upper airways. Patients with a BMI of >30 are transferred to the nutrition and dietetics unit. It is known that a reduction in BMI of 5–10% significantly reduces the AHI [32].

The sleep study is performed using standard polysomnography.

Standard nocturnal polysomnography involves (i) recordings of sleep-related electroencephalography (EEG), electromyography (EMG) of the chin and leg muscles, electrooculography (EOG), and electrocardiography (ECG); (ii) oxygen saturation; and (iii) measures of respiratory effort and airflow.

The tests are used to define PS with an AHI of <5 events/h of sleep, moderate OSAHS as an AHI of 15 to 29.9 events/h of sleep, and severe OSAHS as ≥30 events/h of sleep [eleven].

Laboratory-assisted polysomnography has been and continues to be a gold standard for the diagnosis of sleep-disordered breathing, although the usefulness of a single night-time recording for diagnosis can generate considerable variability in the AHI from night to night, especially when the AHI is low [11].

Therapy with the AirwayGym^®^ application will be initiated after inclusion in this study. This therapy will be applied to patients with an average duration of training of 5 days a week with 15–20 min/session. Three months after myofunctional therapy, an otorhinolaryngological evaluation, sleep questionnaires, and tongue strength measurements with the IOPI and ultrasound will be performed [11].

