The distribution of visits to the center will be as follows:Pulmonology visit: Patients will be diagnosed with OSA in a pulmonology laboratory via an initial sleep study, which includes the measurement of baseline AHI, the nocturnal desaturation index, and the lowest oxygen saturation levels during the night.Otorhinolaryngology visit: Patients will be assessed by the otorhinolaryngologist, who will evaluate the anatomy and functionality of the upper airways using DISE and measure tongue strength with the IOPI and TDS. The AirwayGym app is recommended for patients with oropharyngeal hypotonia.Ultrasound visit: A neck ultrasound will be performed to measure tongue thickness (mm), height (mm), volume (cm^3^), and distance between the lingual arteries (mm) before DISE and at the start of treatment modulation with the app (Figure 4 and Figure 5).Monthly telemedicine follow-up: During the 3-month study period, all patients in the three groups will be monitored for adherence and incidents related to the prescribed treatment with the AirwayGym app.Three-month follow-up: All variables evaluated during the initial visit will be measured again after three months. The ultrasound visit is an evaluation added to this previously published protocol (Tongue +) [36]. A submental ultrasound will be performed in the context of sleep apnea.

The Kolmogorov–Smirnov test will be used for the distribution of quantitative variables. The chi-square test or Fisher test will be used as necessary for the study of categorical variables. Student’s *t*-test or ANOVA (for two or more samples) will be used to study the differences between quantitative variables.

Non-parametric tests (Mann–Whitney or Kruskal–Wallis) will be used if the variables to be analyzed do not follow a normal distribution. The level of statistical significance will be set at *p* < 0.

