Submental ultrasound is a non-invasive technique used to evaluate the size of the genioglossus and geniohyoid muscles, which are important in keeping the upper airway open during sleep. These muscles are located at the bottom of the jaw and are inserted into the tongue and larynx.

In the setting of OSA, submental ultrasound can be used to determine whether the size of these muscles is adequate to keep the upper airway open during sleep. If these muscles are small or weakened, there may be an increased risk of airway obstruction and sleep apnea [44]. Due to MT ameliorating OSA and sensorimotor deficit in selected patients, all clinical information obtained from the muscle pattern can be a useful tool for more accurate future therapeutic decisions [11,45].

We are interested in comparing the results obtained from the anthropometric characteristics of our patients with other populations to verify if there are significant differences between them [46,47].

Despite the strengths of this pilot study mentioned above, we note several limitations. First, the number of participants is small. The number of patients in the control group is low because we found significant differences in the therapy group early during this study. We therefore decided not to enroll more patients in the control group because of the difficulties experienced by patients with severe OSAHS not given appropriate therapy.

There is no blinding since it is a diagnostic protocol. Mood disorders are not analyzed since the exclusion criteria include patients with serious illnesses or those taking treatments that affect apnea.

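### The named t-test and ANOVA assume equal variances, and the stated rule guards only against non-normality, although unequal spread with unequal group sizes is plausible here

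*Protocol article*

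**What the plan says.** The statistical paragraph closes section 4.3. It checks distributions with the Kolmogorov–Smirnov test. For quantitative variables it names Student's t-test or "ANOVA (for two or more samples) will be used to study the differences between quantitative variables". The one route away from these tests is a failed normality check: "Non-parametric tests (Mann–Whitney or Kruskal–Wallis) will be used if the variables to be analyzed do not follow a normal distribution". Mann–Whitney and Kruskal–Wallis compare independent groups, so the paragraph is read here as covering between-group comparisons.

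On the groups, section 2.2 states that "The control group will include patients with recent moderate–severe sleep apnea (1–3 months" on CPAP, while the MT group takes moderate apnea only. Section 4.3 defines "moderate OSAHS as an AHI of 15 to 29.9 events/h of sleep, and severe OSAHS as ≥30 events/h of sleep". Section 4 sets entry at an AHI above 15 and gives no upper limit.

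On group size, section 4.1 plans a pilot "with 15 patients in the control group, 15 patients in the moderate MT apnea group, and 15 patients with MT-CPAP severe apnea", and section 5.2 repeats these numbers. The limitations in section 5.2 then say "The number of patients in the control group is low" and explain the halt in recruitment: "We therefore decided not to enroll more patients in the control group because of the difficulties experienced by patients with severe OSAHS not given appropriate" (quote cut before its last word). No final control number is given, and no standard deviation is given for any outcome.

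**The concern.** Student's t-test and classical ANOVA pool the group variances. With equal group sizes this does little harm. With unequal sizes the pooled variance is dominated by the larger group. If the smaller group has the larger spread, the standard error is too small and the test rejects a true null too often. If the smaller group has the smaller spread, the test is conservative.

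A Kolmogorov–Smirnov check looks at shape and does not detect unequal variance between groups that are each normal. The rank tests used as fall-back are not immune either.

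The design makes this combination plausible. Controls span a wider severity range than the MT group, and their recruitment was stopped. What is at stake is whether a nominal 5% result in the control-versus-MT comparisons of ultrasound and tongue-strength measures can be taken at face value.

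**Working it through.** **Inputs from the article.** Tests: Student's t-test and ANOVA (section 4.3). Planned sizes: 15/15/15 (section 4.1). Severity: MT has AHI 15 to 29.9; controls have AHI above 15 (sections 2.2, 4, 4.3).

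**Assumed inputs.** Two-sided 5%: the text shown breaks off after "The level of statistical significance will be set at" *p* < 0., and section 5.1 uses *p* < 0.05. Control n of 5 to 10, MT n = 15, and the SD ratios below are assumptions. The sample size rests on no SD, effect size or power, so there is no figure of the plan to reproduce beyond 3 × 15 = 45.

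**1. Mechanism.** Set the MT SD to 1 and the control SD to r. The true variance of the mean difference is r²/n + 1/15. The pooled test estimates, on average, [((n − 1)r² + 14)/(n + 13)] × (1/n + 1/15).

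- n = 15, r = 2: true 4/15 + 1/15 = 0.333; pooled 2.5 × 2/15 = 0.333. They agree.
- n = 8, r = 2: true 4/8 + 1/15 = 0.567; pooled (28 + 14)/21 × 0.1917 = 0.383. The standard error is √(0.383/0.567) = 0.82 of what it should be.
- n = 8, r = 0.5: true 0.25/8 + 1/15 = 0.098; pooled (1.75 + 14)/21 × 0.1917 = 0.144. The standard error is √(0.144/0.098) = 1.21 times what it should be.

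**2. Which SD ratios are reasonable.** If AHI were uniform, the SD would be 14.9/√12 = 4.3 in the MT window. For controls it would be 30/√12 = 8.7 over 15 to 45, or 45/√12 = 13.0 over 15 to 60, so the AHI ratio would be 2.0 or 3.0. That does not carry over directly to other outcomes. If an outcome is linear in AHI with correlation ρ in controls, and the AHI ratio is k, the outcome SD ratio is 1/√(ρ²/k² + 1 − ρ²). With k = 3:

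- ρ = 0.3: 1/√(0.01 + 0.91) = 1.04
- ρ = 0.5: 1/√(0.028 + 0.75) = 1.13
- ρ = 0.7: 1/√(0.054 + 0.51) = 1.33

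**3. Type I error of Student's t-test** (normal data, equal means, MT n = 15, 100,000 data sets per cell, %):

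| Control n | ratio 0.5 | 1 | 1.25 | 1.5 | 2 | 3 |
|---|---|---|---|---|---|---|
| 15 | 5.3 | 5.1 | 5.0 | 5.1 | 5.3 | 5.4 |
| 10 | 3.0 | 5.1 | 6.1 | 7.0 | 8.8 | 10.4 |
| 8 | 2.1 | 4.9 | 6.6 | 8.2 | 10.7 | 14.0 |
| 5 | 1.2 | 5.0 | 7.9 | 10.9 | 15.7 | 22.3 |

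At the ratios of 1.13 and 1.33 from step 2, control n of 10 to 5 gives about 5.5% to 9%. The Welch t-test stays at 4.8% to 5.6% in every cell of this table.

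**4. The other named tests.** Three-group ANOVA (control/MT/MT-CPAP) with SDs 2:1:1 gives 6.1%, 9.7% and 16.0% at control n = 15, 10 and 5. With SDs 2:1:2 it gives 5.6%, 6.5% and 8.0%. Mann–Whitney at ratios 2 to 3 gives 6.7% to 8.8% at n = 10 and 8.4% to 10.0% at n = 5.

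**The case against.** A reader might infer that the groups differ in spread by definition, and that the control-versus-MT comparison therefore rejects a true null at two to four times 5%. The article does not support that, for four reasons.

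- **Only baseline AHI differs in spread by definition.** There the group means differ by design too, so a rejection is not a type I error and AHI at entry is no example. Follow-up AHI does not replace it: controls are on CPAP, so the entry window does not fix their later spread.
- **No spread is given for the outcomes of interest.** The ultrasound, IOPI and digital spoon measures have no SDs. Severity may explain only part of their variation, which leads to ratios of about 1.0 to 1.3 and little inflation.
- **The control number is unknown.** Section 5.2 calls it low but gives no count, and the same section restates 15. At 15 v 15 the t-test holds its level.
- **The control group is not described consistently.** Section 2.2 has moderate–severe patients on CPAP. The limitations in section 5.2 explain the halt by severe patients without appropriate therapy. Small size and wide spread may not describe the same group.

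All four stand, and they limit the size. It is also fair to say that an article may leave the version of a t-test to a fuller plan, and that this is an unpowered pilot. That argument is weaker here, because the article does commit to a rule: named tests, and one condition for leaving them. Unequal variance is not part of it.

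**Conclusion.** The point holds as a conditional one. The stated rule protects against non-normality only, and the design makes unequal spread with unequal group sizes plausible. The pooled tests may then not hold 5%, and the direction depends on which group has the wider spread.

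With 15 MT patients and 5 to 10 controls, type I error is about 5.5% to 9% at SD ratios of 1.1 to 1.3, about 9% to 22% at ratios of 2 to 3, and about 1% to 3% at a ratio of 0.5. It stays near 5% if 15 controls were reached. These ranges rest on assumed control numbers, assumed SD ratios and normal data. The article does not show which row applies, so no single multiple of 5% should be quoted. This is a cheap improvement, not a flaw that undermines the study.

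**What to change.** In the statistical paragraph of section 4.3, name the Welch t-test (two groups) and Welch ANOVA (three groups), with Games-Howell for pairwise contrasts, as the default for between-group comparisons of quantitative variables. Use them always, not after a variance pre-test. Report the actual number in each group with every test.

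The cost is one sentence, with no extra data or patients. If the variances are in fact equal, the power loss in simulation is about 0 to 2 percentage points at control n of 8 to 15. It can reach about 5 to 9 points at control n = 5, depending on the true difference. At control n = 3 Welch itself drifts to about 7%, so a control group that small would need caution under any test.

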MRI is the most commonly used imaging method to measure volumes and obstruction in the upper airways. Recent studies have incorporated computed tomography with the patient under sedation [14] and ultrasound. Ultrasound is a non-invasive, low-risk, and cost-effective imaging modality that can also be used to assess the tongue. Submental ultrasound can be used to characterize the tongue in patients with OSA and has shown that an increased width and thickness of the tongue are associated with severe OSA [15,16]. Ultrasound can also be used to examine the dynamic movements that characterize changes in tongue morphology with activities such as the Müller maneuver [17,18]. Yu et al. [19] reported that the ultrasound echo intensity increases with increasing fat content in the tongue and strongly correlates with tongue fat measurements in MRI.

In the context of OSA, submental ultrasound can be used to determine whether the size of the tongue muscles is adequate to keep the upper airways open during sleep. Small or weak muscles may increase the risk of airway obstruction and sleep apnea [20]. MT can increase the size and strength of the genioglossus and geniohyoid muscles, which helps to improve upper airway function and reduce the severity of OSA.

Myofunctional therapy (MT) is based on oropharyngeal exercises that try to obtain a proper tongue positioning in the oral cavity. Guimaraes [21] in his randomized clinical trial (RCT) demonstrated that oropharyngeal exercises reduced the OSAS severity from an apnea–hypopnea index (AHI) of 22.4 +/− 4.8 to 3.7 +/− 8.5 events/hour. MT is composed of isotonic and isometric exercises that target oral structures (i.e., the lips and tongue) and oropharyngeal structures (i.e., the soft palate and lateral pharyngeal wall). There has been an increasing number of studies evaluating the effect of MT in the form of case studies, case series, and, most recently, two RCTs [12,22,23,24,25,26]. Because MT raises serious concerns relating to adherence, our sleep unit has designed the AirwayGym app to perform these exercises.

Using this protocol, we can examine the usefulness of ultrasound in predicting the treatment response to MT delivered by specialists using the AirwayGym application employed in our sleep unit.

The AirwayGym application was created in 2018 by the Sleep Units of the Quiron Salud Marbella and Campo de Gibraltar Hospital together with the computer engineering departments and developed by the apnea company Bye.

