### 2.3. Objectives

-To evaluate the influence of MT on the reduction in cervical fat and the improvement of ultrasound parameters in sleep apnea.-To measure different parameters related to the function and size of the genioglossus and geniohyoid muscles to evaluate the presence and severity of sleep apnea, as well as the effectiveness of myofunctional therapy in improving the function of these muscles.-To determine whether performing a neck ultrasound is relevant for the indication of TM in sleep apnea.-To evaluate whether performing ultrasound and DISE modify the indication of surgical techniques compared with if we only performed DISE.-To evaluate the adherence to CPAP and MT.

The hypothesis of our work is based on determining whether knowledge of the fatty and muscular components can be decisive in the choice of pharyngoplasty techniques, in multilevel surgery, and as a possible predictor of response or failure to MT since, currently, the influence that TM can have on reducing cervical fat is unknown.

Given that the aforementioned tools only measure strength, we consider the previous study of cervical fat using ultrasound and its response to TM relevant in the study of collapse patterns during DISE.

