### 5.1. Preliminary Results

Additionally, submental ultrasound may be useful to evaluate the effectiveness of MT in sleep apnea. Studies have shown that myofunctional therapy can increase the size and strength of the genioglossus and geniohyoid muscles, which can improve upper airway function and reduce sleep apnea. Submental ultrasound can be used to measure these muscle changes and evaluate the effectiveness of therapy. With 10% of the patients included, there were significant differences (*p* < 0.05) in the initial volume (mm^3^) and lingual thickness (mm) between the control patients and the patients in the groups with moderate–severe sleep apnea. After 3 months of myofunctional therapy, we found a statistically significant improvement in the values of the functional examination with IOPI and the digital spoon and a reduction in lingual thickness (mm) of >15% in the patients studied.

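### Ultrasound is to be examined as a predictor of response to MT, but the listed tests reach that aim only through an undefined responder split, and no measure of prediction is named

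*Protocol article*

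**What the plan says.** Prediction is a declared aim in three places of the protocol article. The Introduction says that with this protocol "we can examine the usefulness of ultrasound in predicting the treatment response to MT". The hypothesis in section 2.3 treats knowledge of the fatty and muscular components "as a possible predictor of response or failure to MT", and the Discussion (section 5.2) repeats this. The third objective in section 2.3 asks whether neck ultrasound matters for deciding on MT.

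The statistical paragraph at the end of section 4.3 lists these methods:

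- Kolmogorov–Smirnov: this "test will be used for the distribution of quantitative variables".
- Chi-square or Fisher: "The chi-square test or Fisher test will be used as necessary for the study of categorical variables".
- Student's t-test or ANOVA: these "will be used to study the differences between quantitative variables".
- Mann–Whitney or Kruskal–Wallis: these "will be used if the variables to be analyzed do not follow a normal distribution".

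The paragraph does not say which variable forms the groups. Correlation, regression, ROC curves and accuracy measures are not mentioned, and no section defines response to MT. Section 4.1 plans 15 patients in each of three groups. Sections 2 and 2.2 describe a non-randomised study with CPAP controls (moderate–severe apnea), an MT group (moderate) and an MT-CPAP group (severe).

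**The concern.** A prediction question concerns individuals: among patients who receive MT, does the baseline ultrasound value relate to that patient's later response? Its null hypothesis is no such relation. A test between study arms has another null, namely that the arms have the same mean or distribution. Rejecting or keeping the second null says nothing about the first.

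The arms make this worse. They are not randomised, and the two MT arms are separated by severity. The Introduction itself ties greater tongue width and thickness to severe apnea. An ultrasound difference between arms is therefore expected from case mix alone.

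At stake is the predictor hypothesis and the third objective. Followed as written, the analysis could end with no usable estimate of how well ultrasound predicts response, or with one that depends on a response cut chosen after the data are seen.

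**Working it through.** **The plan's own figure.** Section 4.1 gives a pilot size without alpha, power, effect size or SD. Only the sum can be checked: 3 × 15 = 45 patients, of whom 15 + 15 = 30 receive MT.

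**Assumptions, not document values.** Two-sided alpha is 0.05; the level in section 4.3 is cut off in the text at hand, and section 5.1 uses 0.05. There is one ultrasound marker, with correlation r = 0.3, 0.5 or 0.7 between its baseline value and response. Nothing is adjusted for. Responders are those above the population median of response. Baseline ultrasound means are equal in the three arms.

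**Simulation.** 4,000 trials per setting at 15/15/15 gave these chances of p < 0.05:

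| Analysis | r = 0.3 | r = 0.5 | r = 0.7 |
|---|---|---|---|
| ANOVA of baseline ultrasound across the three arms | 5% | 5% | 5% |
| Mann–Whitney, responders v non-responders (30 MT patients) | 23% | 58% | 93% |
| t-test, same split | 25% | 61% | 94% |
| Correlation of baseline ultrasound with response (30 MT patients) | 36% | 83% | 99% |

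The comparison of arms stays at its error rate however strong the predictor is. If the arm means did differ by severity, it would reject more often, but for a reason unrelated to prediction.

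**Check of the continuous analysis by formula.** Power ≈ Φ(atanh(r) × √(n − 3) − 1.96).

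- n = 30, r = 0.5: 0.549 × √27 − 1.96 = 2.854 − 1.96 = 0.894, so 81% (simulated 83%).
- n = 15 (one MT arm), r = 0.5: 0.549 × √12 − 1.96 = 1.903 − 1.96 = −0.057, so 48%.

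**Check of the split by formula.** Cutting a normal response at its median multiplies the correlation by √(2/π) = 0.798, so 0.5 becomes 0.399. Then 0.422 × √27 − 1.96 = 2.194 − 1.96 = 0.234, so 59% (simulated 61%).

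**What the split can detect.** For a difference of d SD in baseline ultrasound between responders and non-responders, AUC = Φ(d/√2). Power of the t-test from the non-central t distribution:

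| Split | d = 0.8 (AUC 0.71) | d = 1.0 (AUC 0.76) | d = 1.2 (AUC 0.80) |
|---|---|---|---|
| 15 / 15 | 56% | 75% | 89% |
| 10 / 20 | 51% | 70% | 85% |
| 8 / 7 (one MT arm) | 30% | 43% | 57% |

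**Precision of the proposed analysis.** 95% interval = tanh(atanh(r) ± 1.96/√(n − 3)). For r = 0.5 and n = 30: tanh(0.549 ± 0.377) = 0.17 to 0.73.

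**The case against.** The strongest reply has four parts.

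1. **The listed tests can address prediction.** Nothing confines them to the study arms. A Mann–Whitney test of baseline ultrasound by responder status yields the AUC (U divided by n1 × n2), and Fisher's test handles marker status against response. This stands. A reader might infer that every listed test compares group means, or that a real predictor is bound to be missed. Neither is supported: Kolmogorov–Smirnov, chi-square, Fisher and the rank tests do not compare means, and the split detects a predictor of r = 0.7 in 94% of trials. What remains is that the split needs a response cut that no section gives, and that it loses power.

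2. **Most aims are about change or difference.** The first objective is "To evaluate the influence of MT on the reduction in cervical fat and the improvement of ultrasound parameters in sleep apnea", and a test of mean change suits it. This also stands, and the point is limited to the predictor aim. A reader might take section 5.1, with "a reduction in lingual thickness (mm) of >15% in the patients studied", as a claim of prediction already drawn from a mean fall. The text does not support that: the section speaks of evaluating how well MT works, which is monitoring.

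3. **A condensed article may leave the model to a full protocol or SAP.** A missing model alone would be no finding. But this article does state its methods, and those assigned to quantitative variables are tests of difference that do not match the hypothesis it also states.

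4. **A regression has weaknesses of its own.** Change in the MT-CPAP group cannot be credited to MT alone, IOPI measures only strength, several markers raise multiplicity, and the 83% is for one unadjusted correlation. All of this is fair. It shapes the fix and limits the claim, but does not restore the listed tests as a direct answer.

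**Conclusion.** The stated analysis is not tied to the stated prediction aim. Comparisons between the non-randomised, severity-related arms cannot answer it. The listed tests can, but only through a responder split whose cut is undefined. At an assumed r = 0.5 with 30 MT patients, the split has about 61% power against about 83% for a continuous analysis. Both figures rest on one marker, no adjustment, a median cut and two-sided alpha 0.05. In one MT arm of 15, even the continuous analysis has only about 48%. The direction of the loss holds at all three values of r examined; its size depends on r. The objectives on change and difference are not affected. The point is worth correcting before analysis.

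**What to change.** In the statistical paragraph of section 4.3, add for the predictor aim:

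- An exploratory regression in the patients receiving MT (planned n = 30) of the 3-month value of a response measure named in advance, for example IOPI tongue pressure, on each baseline ultrasound measure. Adjust for the baseline value of that response measure and for group (MT or MT-CPAP).
- Slopes and partial correlations with 95% confidence intervals for all ultrasound measures, not a selection.
- Results also by group, because change in the MT-CPAP group cannot be attributed to MT alone.
- A sentence stating that mean differences between arms or over time are not evidence of prediction.

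The cost is a few lines of text and a small set of regressions. Section 4.3 already plans IOPI and ultrasound at baseline and 3 months, so no patients or procedures are added. The downside is wide intervals (about 0.17 to 0.73 for r = 0.5 at n = 30, before adjustment) and several markers, so the result can only generate hypotheses.

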### 4.2. Definition of Variables

The variables that we will measure in all patients and that are reflected in the data collection table using IBM SPSS Statistics version 28 with Windows software are as follows:Age;Sex;Weight;Height;BMI;Abdominal circumference (at the level of the navel);Neck circumference (with a flexible tape on the most prominent part; for this, it is necessary for the patient to be standing, with arms hanging at the sides, head erect, and gaze forward);Measurement with IOPI of tongue force and buccinator muscle;Measurement with digital spoon (DS);Initial AHI;Ranking of velum, oropharynx, tongue base, and epiglottis (VOTE) in DISE, before and after;Ultrasound measurements: echo intensity, tongue height (mm), and tongue width (mm).

To develop the protocol, patients with sleep apnea underwent submental cervical ultrasound and DISE before starting to use the AirwayGym app (www.airwaygym.app, accessed on 27 January 2024) and after 3 months of treatment.

The AirwayGym app is a portable fitness app (Figure 2) intended for patients rather than athletes, and therapists rather than coaches provide the instructions. The novelty of this app is that it is the first healthcare app on the market that allows patients to directly interact with a smartphone without the need for any other device. The app focuses on improving proprioceptive deficits in patients with sleep apnea. When used with the app, the smartphone provides acoustic feedback on the effectiveness of the MT exercises performed [27].

The AirwayGym app comprises daily tension and concentration exercises (i.e., isometric and isotonic exercises, respectively) that can be performed anywhere. It offers the additional advantage of providing prompt feedback to allow patients to see their progress and resolve problems with the help of a therapist. Before each exercise, an animated demonstration and video provide instructions for performing the exercise. After each exercise, patients receive visual, acoustic, and tactile feedback as a score on the success of their performance. A chat function is available via which patients can contact the therapist directly. This app complies with regulations 2002/58/EC and (EU) 2016/679 regarding data protection. It is priced at EUR 8.99. Additional information can be found on the AirwayGym website.

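### The plan names no paired test: its categorical and rank tests are for independent samples, although every variable is measured at baseline and at 3 months in the same patients

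*Protocol article*

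**What the plan says.** The statistical paragraph closes section 4.3 of the protocol article. It has four parts:

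- A Kolmogorov–Smirnov test is used for the distribution of quantitative variables.
- For categorical data, "The chi-square test or Fisher test will be used as necessary for the study of categorical variables".
- For quantitative data, Student's t-test or "ANOVA (for two or more samples) will be used to study the differences between quantitative variables".
- As the fallback, "Non-parametric tests (Mann–Whitney or Kruskal–Wallis) will be used if the variables to be analyzed do not follow a normal distribution".

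The paragraph ends with "The level of statistical significance will be set at" p < 0., with no digits after the point.

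The same section describes a repeated-measures design: "All variables evaluated during the initial visit will be measured again after three months". Section 4.2 lists the endoscopic classification as "epiglottis (VOTE) in DISE, before and after". The first objective in section 2.3 is "To evaluate the influence of MT on the reduction in cervical fat and the improvement of ultrasound parameters in sleep apnea". The hypothesis in section 5.2 concerns tongue function before and after the exercises. Section 4.1 plans 15 patients in each of three groups.

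**The concern.** A baseline and a 3-month value from one patient are correlated. The test of change has to use that, by working on within-patient differences or on discordant pairs. Mann–Whitney, Kruskal–Wallis, chi-square and Fisher treat the two sets of values as coming from different people. For a before/after comparison of VOTE, or of any quantitative variable judged non-normal, the plan names nothing that fits. For a normally distributed variable it leaves open which form of t-test or ANOVA is meant.

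If an analyst follows the named tests on the before/after question, the standard error is too large and the p-value too high. With 15 patients per group, a real change could then be reported as no change. Section 1 says that favourable findings would open the way to further clinical trials, so a missed change has consequences beyond this pilot.

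**Working it through.** **Inputs from the document.** There are 15 patients per group (section 4.1), measured at two time points (section 4.3). The level of 0.05 is the one used in section 5.1. The article gives no power, SD, effect size or correlation, so there is no figure of its own to reproduce.

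**Assumptions.** Values are bivariate normal with equal SD at both visits. The change is 0.6 SD. The baseline to 3-month correlation ρ is 0.5, 0.7 or 0.9. Tests are two-sided at 0.05.

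**Standard error of the mean change, in SD units.**

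- Treated as independent: √(2/15) = 0.365.
- Paired: √(2(1−ρ)/15) = 0.258, 0.200 and 0.115 for ρ = 0.5, 0.7 and 0.9.
- Ratio: 1/√(1−ρ) = 1.41, 1.83 and 3.16.

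**Power and true size.** Paired power comes from the noncentral t distribution with 14 degrees of freedom and noncentrality 0.6/SE = 2.32, 3.00 and 5.20. Figures for the independent t-test come from simulation (200,000 runs per setting).

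| ρ | Power, independent t | Power, paired t | True size of nominal 5% independent t |
|---|---|---|---|
| 0.5 | 31% | 58% | 0.8% |
| 0.7 | 28% | 80% | about 0.1% |
| 0.9 | 22% | 99.8% | near 0% |

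In the same runs without any true change, the paired t-test rejected in about 5%.

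**Rank tests, the plan's stated fallback.** For a change of 0.5 SD and n = 15, simulated power was:

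| ρ | Mann–Whitney | Wilcoxon signed-rank |
|---|---|---|
| 0.5 | 18% | 41% |
| 0.7 | 14% | 64% |
| 0.9 | 10% | 97% |

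**Categorical outcome, illustrative counts only.** Suppose obstruction at one VOTE site is present in 10 of 15 patients before and 4 of 15 after, with six improving and none worsening.

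- Fisher on the table (10, 5; 4, 11) gives p = 0.066.
- Exact McNemar on six against zero discordant pairs gives 2 × 0.5⁶ = 0.031.

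The data are the same, and the conclusion at 0.05 differs.

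**The case against.** **The t-test and ANOVA may be meant as paired.** A paired t-test is a Student's t-test, and ANOVA can be repeated-measures. A reader might infer that every listed test is for independent samples, but the text does not establish that. The bracketed reference to two or more samples and the choice of fallbacks only point that way. This part of the objection stands. It does not reach the rank and categorical tests, which have no paired form under those names.

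**The listed tests suit other questions in the study.** There are three groups, and section 5.1 reports a comparison of initial values between groups. The named tests fit that, and would fit change scores compared between groups. This also stands. However, the article does not say that change scores are analysed, and it does not confine the tests to between-group use.

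**An article condenses a fuller plan.** Much detail may properly sit elsewhere. Here, though, the article goes as far as fixing named tests and a named fallback, and for a central before/after question they do not fit.

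**The p < 0. threshold.** Read literally, no result could meet it. The likelier explanation is digits lost in print or in reading the PDF, since section 5.1 uses 0.05. It is not a methodological error.

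**Kolmogorov–Smirnov.** A reader might infer that the normality check is nearly powerless at n = 15. That depends on the uncorrected form being used on raw values within each group. The article states neither the form nor what it is applied to, so the point does not carry weight.

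**Baseline adjustment between groups.** A large gain in precision from ANCOVA might be inferred. The usual formula assumes that baseline is unrelated to group. Here the groups are non-randomised and partly defined by severity (section 2.2), so that gain cannot be promised, and adjustment would not remove confounding.

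**Conclusion.** The concern holds for the tests that are named. Chi-square, Fisher, Mann–Whitney and Kruskal–Wallis do not suit before/after data from the same patients, and no paired alternative is given. The t-test and ANOVA are unspecified rather than wrong.

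Misapplied before versus after, the tests would be conservative. They would not inflate false positives within groups as long as the two visits are positively correlated. The cost is power: over correlations of 0.5 to 0.9, 22–31% instead of 58% to more than 99% for a 0.6 SD change in 15 patients. The effect size and correlations are assumptions, so the direction is firm and the exact loss is not. The VOTE counts only illustrate that the choice of test can change the conclusion.

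This is worth correcting before the analysis. It does not show that any reported result is wrong, because section 5.1 does not say which test produced its before/after findings.

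**What to change.** Rewrite the statistical paragraph in section 4.3 to state:

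- **Within group, quantitative:** paired t-test, or Wilcoxon signed-rank if the changes are clearly non-normal.
- **Within group, VOTE:** McNemar for a two-category outcome, or signed-rank on the grade.
- **Between groups at baseline:** the tests already listed.
- **Between groups at 3 months:** change scores or baseline-adjusted values, chosen in advance, with 95% confidence intervals. Add a sentence that adjustment does not remove confounding, because the groups are non-randomised and partly defined by severity.
- **Normality:** judged on within-patient changes or model residuals.
- **Significance level:** confirm that the truncated threshold reads two-sided 0.05, in line with section 5.1.

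The cost is one rewritten paragraph. No new data, visits or patients are needed.
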